## Abstract

**Background:**

There is evidence that exposure to passive smoking in general, and in babies in particular, is an important cause of morbimortality. Passive smoking is related to an increased risk of pediatric diseases such as sudden death syndrome, acute respiratory diseases, worsening of asthma, acute-chronic middle ear disease and slowing of lung growth.

The objective of this article is to describe the BIBE study protocol. The BIBE study aims to determine the effectiveness of a brief intervention within the context of Primary Care, directed to mothers and fathers that smoke, in order to reduce the exposure of babies to passive smoking (ETS).

**Methods/Design:**

Cluster randomized field trial (control and intervention group), multicentric and open. Subject: Fathers and/or mothers who are smokers and their babies (under 18 months) that attend pediatric services in Primary Care in Catalonia.

The measurements will be taken at three points in time, in each of the fathers and/or mothers who respond to a questionnaire regarding their baby's clinical background and characteristics of the baby's exposure, together with variables related to the parents' tobacco consumption. A hair sample of the baby will be taken at the beginning of the study and at six months after the initial visit (biological determination of nicotine). The intervention group will apply a brief intervention in passive smoking after specific training and the control group will apply the habitual care.

**Discussion:**

Exposure to ETS is an avoidable factor related to infant morbimortality. Interventions to reduce exposure to ETS in babies are potentially beneficial for their health.

The BIBE study evaluates an intervention to reduce exposure to ETS that takes advantage of pediatric visits. Interventions in the form of advice, conducted by pediatric professionals, are an excellent opportunity for prevention and protection of infants against the harmful effects of ETS.

**Trial Registration:**

Clinical Trials.gov Identifier: NCT00788996.

## Background

Environmental tobacco smoke (ETS) consists of a mixture of smoke produced by the burning of cigarettes and the smoke directly exhaled by smokers. A large part of the smoke that is inhaled by a passive smoker is made by the burning of cigarettes, which contains certain toxic components at levels far above those inhaled by the actual smoker. It has been shown that the levels of nicotine and tar produced by burning cigarettes are three times higher than in the smoke directly exhaled by smokers, and the concentration of carbon monoxide (CO) approximately five times higher [1]. In addition, the spontaneous burning of cigarettes produces smaller particles that are able to penetrate deeper areas of the lungs [2].

Since the milestone publication by Doll and Hill in 1950, it has been known that tobacco is harmful to health [3], but until 1974 no one had talked about smoking in fathers/mothers, ETS and the consequences for children. Currently, we have evidence [4] that the smoking in parents is associated with various adverse effects on infant health: increased risk of sudden infant death syndrome [5], acute respiratory diseases, respiratory symptoms, aggravation of symptoms in patients with asthma, acute and chronic diseases in the middle ear and slowed lung growth [6,7]. Passive smoking is the leading cause of preventable death in infancy in industrialized countries (third cause of preventable death in adults). According to the International Agency for the Research on Cancer (IARC) of the World Health Organization (WHO), second hand smoke is a type A carcinogen [8]. Furthermore, the WHO MPOWER report [9] proposes suggestive evidence between environmental exposure to tobacco smoke and the following diseases: leukemia, lymphoma, brain tumors and asthma. It is particularly worrying in younger children because they are dependent on adults and therefore cannot avoid exposure to tobacco smoke; moreover, their immune systems are underdeveloped.

In Spain, the law on tobacco control measures (28/2005) has led to notable progress in reducing ETS in work places and in increasing the awareness of the damage caused by ETS [10]; however, at the same time this law has made the home one of the few places where people can smoke [11]. As an example of the exceptions and contradictions of the Spanish law, in "small" places of entertainment (less than 100 square meters) such as bars and restaurants, the owners can decide whether or not to apply a smoke-free policy. Preliminary estimates indicate that 90-95% of small establishments have opted to allow smoking, furthermore, the Spanish law permits the access of children who go in the company of their parents [12]. In Catalonia, various interventions have been carried out to reinforce smoking cessation during pregnancy [13,14]. ETS has the greatest effect on the health of children under the age of five, given that this group of individuals tends to spend the most time at home, making them the most vulnerable to the effects of passive smoking [15-17]. There are few studies on measures to reduce ETS in the home [18]. Various studies have shown that the potential for tobacco pollution at home is more significant than levels of atmospheric contamination. Nonetheless, up to 75% of mothers that smoke expose their newborns to smoke, and between 47-60% of their babies present significant levels of urinary cotinine [19,20].

Interventions to reduce passive smoking have obtained irregular results [21-26]. The Cochrane review [27] on the subject states that there is no sufficient evidence to support any one intervention's effectiveness in reducing smoking habit in parents and the exposure in children. Various studies have established that the level of nicotine in hair is a good quantitative indicator to measure the environmental exposure of tobacco smoke [28-32].

Health education messages from pediatric professionals are an excellent opportunity and, in general, are well accepted by parents since they make reference to the health of their son or daughter. Brief interventions, according to the context and impact of the content, can be just as effective as more intensive interventions [33]. Studies about this type of intervention have not been published in our country.

It is important to conduct methodologically sound studies with a more appropriate design (especially in the calculation of the sample size and monitoring) and evaluation through objective measure of results, such as the level of nicotine in hair.

### Objectives

The principle objective of the BIBE study is to determine the effectiveness of a brief intervention directed at fathers and/or mothers that smoke in order to reduce ETS in babies, in the context of pediatric visits in primary care.

The secondary objectives of the BIBE study are to determine if this intervention produces changes in the tobacco consumption of the parents and subsequently, to study the concordance between the subjective measures of ETS and the objective measures (questionnaire versus biological analysis of nicotine in hair).

The specific objective of this article is to describe the protocol of the BIBE study.

## Methods/Design

### Study design

Multi-centric, open cluster randomized field trial. Unit of randomization: Primary Care teams formed by a pediatrician and a pediatric nurse, both responsible for the same infant population.

### Setting

Pediatric Primary Care consultations in Catalonia. All of the basic health areas of Catalonia will be offered participation through the *xarxa de centres sense fum *(network of smoke free centers).

### Study period

The preparation and pilot test period: during 2008

Data collection period: March-December 2009. The period is not coincidental; the first recruitment visit is in spring and the six-month control visit in the fall, in order to compare the degree of exposure in a similar climate period.

### Study population

The study subjects are babies under 18 months of age at the time of recruitment, with a mother and/or father that is an active smoker and that attend a pediatric consultation (with the doctor or nurse) in Primary Care for a check-up visit. Figure 1 shows the diagram flow of the study.

**Figure 1 F1:**
[figure not shown]
**Flow diagram of the BIBE study**. Diagram and flow chart of the BIBE study.

### Sampling strategy

During the two-month recruitment period, and until obtaining the eight proposed cases in each team, all of the mothers and/or fathers that visit with a baby under the age of 18 months will be asked whether or not they are smokers.

### Inclusion criteria

Babies under 18 months of age whose parents answer affirmatively to the question "Do you or your partner smoke?" and who give their informed consent to participate in the study.

### Exclusion criteria

- Any pathology or condition that makes inclusion/follow-up difficult at three and six-months (at the professional's criteria), for example parent or baby with an active, acute disease, known addiction in the parents to other substances or foreseeable change in residency.

- Parent in smoking cessation process at the recruitment phase of the study.

- Refusal of parents to participate in the study.

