### Description of the intervention

Once the teams have shown interest in collaborating in the study, the participating teams will be randomly assigned by clusters to the intervention or control group, as specified in the methodology.

There will be three visits (at the start of the study, at three and six months after inclusion in the study for each baby included in the study (control and intervention group). These visits will be used to collect necessary information.

The teams included in the intervention group will be given a two-hour specific training on passive smoking, epidemiology, morbimortality and how to intervene in the reduction of ETS. The proposed intervention is based on interventions recommended in primary care that follow international and national clinical practice guidelines [13,35,36]. The intervention is based on counseling, cognitive theory and motivational interviewing.

Thus, this study is proposing a passive smoking intervention that has been adapted from an intervention that has been shown to be effective in decreasing active tobacco consumption in Primary Care.

The intervention aims to give parents that smoke brief information that emphasizes the health benefits that reducing ETS can have on their children. The basic elements of the intervention include:

1. Ask: whether or not there is a smoker that lives with the baby. If the answer is affirmative, the baby's level of exposure will be asked.

2. Assess knowledge: Information that the parents have about the effect of passive smoking in infancy.

3. Personalized information depending on the exposure and the perceived risk.

4. Ask about suggestions to make changes: support any efforts to modify exposure to ETS and discuss the problems this entails.

5. Personalized help and advice according to exposure, baby's background, perceived risk and parents' attitude towards making changes. This intervention will be reinforced with educational leaflets about passive smoking in infancy designed for the study (Additional file 3).

6. Congratulate if the mother and/or father has quit smoking during the pregnancy and support-encourage continued smoking cessation.

7. Support and encourage those that decide to quit smoking or reduce tobacco consumption.

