## Results

Primary results to obtain:

Reduction of exposure to ETS measured at the beginning of the intervention (recruitment phase) and at six months, using a questionnaire that includes information about ETS history during pregnancy and breastfeeding, exposure to ETS within and outside of the home, family smoking habits and measures used to avoid exposure. To develop this questionnaire, questionnaires used in similar studies have been adapted (varying some items, based on the results of the pilot study). As an objective measurement of the exposure: biological levels of nicotine in hair of babies. All of the hair samples (from the pilot test and the definitive study) will be analyzed by the same team at IMIM.

Secondary results to obtain:

- Reduction or cessation of smoking habit in parents, measured using a questionnaire about status of the smoker/ex-smoker/non-smoker and using the Fagerström Nicotine Dependence Test in those that smoke, as well as the stage of change (pre-contemplation, contemplation, preparation, action, maintenance, finalization). In smokers that declare smoking abstinence, the amount of carbon monoxide in expired air will be determined (Smokerlyzer). Cut-off point: 10 ppm.

-Other variables using questionnaire/clinical records, including data related to:

Type of professional that performs the intervention: pediatrician, pediatric nurse or both.

The baby: age, sex, breastfeeding, medical history, living nucleus.

The father and/or mother that attends the visit: age, sex, marital status, socioeconomic situation.

Parents' level of knowledge and their level of risk perception to exposure.

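### Teams that know their arm recruit the babies under an open-ended exclusion, so enrolment can differ by arm in either direction; baseline measures reduce this risk but do not remove it

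*Protocol article*

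**What the plan says.** The protocol article gives the sequence in several places.

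- **Study design:** the trial is a "Multi-centric, open cluster randomized field trial". The randomised units are "Primary Care teams formed by a pediatrician and a pediatric nurse, both responsible for the same infant population".
- **Description of the intervention:** "Once the teams have shown interest in collaborating in the study, the participating teams will be randomly assigned by clusters". Then "The teams included in the intervention group will be given a two-hour specific training on passive smoking"; control teams are given no such training.
- **Sampling strategy and Sample size:** every parent attending with a baby in the age range is asked about smoking during a two-month window, "until obtaining the eight proposed cases in each team". The care unit itself does the recruiting.
- **Exclusion criteria:** the first criterion is "Any pathology or condition that makes inclusion/follow-up difficult at three and six-months (at the professional's criteria", followed by illustrations (acute illness in parent or baby, other addiction in the parents, an expected move). Separate criteria cover a parent already in the process of quitting, and refusal.
- **Results:** exposure is "measured at the beginning of the intervention (recruitment phase) and at six months", which places the start of the intervention in the recruitment phase.

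On the protective side, Data collection procedures takes hair at recruitment and at six months. Statistical analysis plans a baseline comparability check and comparisons with and without adjustment for known confounders, and stage of change is in that list. The multilevel model for hair nicotine is to contain age, sex and whatever is significant in bivariate analyses.

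**The concern.** Randomising teams balances the teams. It balances the babies only if enrolment does not depend on the arm. Here allocation precedes enrolment, the design is open, and one arm has just been trained in the topic that the outcome measures. The recruiters can therefore be taken to know their arm when they judge whether a family is hard to include or follow up, when they decide whether a parent counts as already quitting, and when they seek consent.

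If those judgements differ by arm, the arms can differ at baseline in exposure, in readiness to change, or in both. The direction cannot be predicted. Trained teams might pass over families who look hard to work with, which would favour the intervention. They might instead seek out heavily exposed babies, which would work against it. At stake is whether a difference in hair nicotine, or the lack of one, can be put down to the intervention.

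**Working it through.** **1. Do recruiters know their arm?** No single sentence says so. It follows from four statements taken together: allocation at team level on volunteering, an open design, training in one arm only, and an intervention that begins in the recruitment phase.

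**2. Which steps leave room for judgement?** Asking all attending parents about smoking makes screening consecutive. It does not govern the discretionary exclusion, the quitting exclusion or the approach to consent, all of which come after the question is asked.

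**3. The plan's own figure.** Inputs from Sample size: mean 6.83 ng/mg, SD 8.88 ng/mg, 30% difference, alpha 0.05, power 80%. Tests are two-sided (Statistical analysis).

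- Target difference: 0.30 × 6.83 = 2.049 ng/mg.
- n per group = 2 × [(1.960 + 0.842) × 8.88 / 2.049]² = 294.8, so 295. The stated figure reproduces.

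295 is used below because the plan's later inflation for loss and clustering is meant to preserve that amount of information.

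**4. Unadjusted six-month comparison, no true effect.** The documents give no size for a selection shift, so it is an assumption and a range is shown.

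- SE = 8.88 × √(2/295) = 0.731 ng/mg.
- A 10% shift is 0.683 ng/mg, one third of the target. Shift/SE = 0.934.
- Rejection rate = Φ(−1.96 + 0.934) + Φ(−1.96 − 0.934) = 0.152 + 0.002 = 0.154.
- If the same shift hides a true 30% effect: (2.049 − 0.683)/0.731 = 1.868, and power = Φ(1.868 − 1.96) = 0.46.

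| Assumed shift | ng/mg | Rejection with no true effect | Power if a true 30% effect is hidden |
|---|---|---|---|
| 0% | 0 | 5% | 80% |
| 5% | 0.34 | 7.5% | 65% |
| 10% | 0.68 | 15% | 46% |
| 15% | 1.02 | 29% | 29% |
| 20% | 1.37 | 46% | 15% |

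**5. The same 10% shift when baseline nicotine is used.** Assume the shift is equal at both visits, the SD is the same at both, and the baseline–follow-up correlation is ρ. Regression on baseline leaves a bias of 0.683 × (1 − ρ), with SE 0.731 × √(1 − ρ²).

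- ρ = 0.5: 0.342/0.633 = 0.539, rejection rate 8.4%.
- ρ = 0.7: 0.205/0.522 = 0.392, rejection rate 6.8%.
- Change score: the shift cancels, rejection rate 5%.

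**6. How much selection makes a shift of that order?** Suppose one arm leaves out 10% of eligible families whose mean is twice the average. That arm's mean becomes (6.83 − 0.10 × 2 × 6.83)/0.90 = 6.07 ng/mg. This is 0.76 ng/mg or 11% lower, and 0.76/2.049 = 37% of the planned effect.

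**The case against.** The strongest reply is that the exclusion is about feasibility, not receptiveness. Its wording and examples concern difficulty of inclusion or follow-up, so leaving out a family because it seems unlikely to respond would arguably misapply the rule. That stands: the clause gives no general licence to pick families. What remains is that no closed list bounds the judgement, and that a person who knows the arm makes it.

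Second, the plan measures much of what matters. Stage of change is a baseline confounder, parents' knowledge and risk perception are recorded, comparability is checked, and hair is sampled at recruitment. This also stands, and it limits the size of the problem, as step 5 shows. It is incomplete for two reasons. Baseline nicotine appears neither among the listed confounders nor by name in the multilevel model. And a family's readiness to change, as sensed by the professional, may affect the change in exposure beyond what stage of change captures.

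Third, the article is condensed and its flow diagram is not shown. The lack of a described screening log, or of a sentence in Limitations, is therefore not counted against the plan.

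A reader might go further and infer that randomisation gives no protection here, that the bias must favour the intervention, or that the false-positive rate is 15%. The documents support none of these. Teams are still randomised and baseline data are collected, no text fixes a direction, and 15% belongs to one assumed shift in an analysis that ignores baseline.

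**Conclusion.** The concern holds as a risk, not as a demonstrated bias. The stated order of events and one open-ended exclusion allow enrolment to differ by arm, in either direction. The planned baseline data reduce the consequences without removing them.

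How much this matters depends chiefly on whether the primary analysis uses baseline nicotine, which the analysis section does not fix. The 10% shift and the correlations are assumptions, as is an equal shift at both visits. Selection on readiness to change would break that last assumption, and then neither baseline regression nor a change score would remove all of the bias. The point should be acted on because the change is cheap, but it does not invalidate the design.

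**What to change.** - Replace the appeal to the professional's judgement and the open list of examples with a closed list of exclusions, answered yes or no in the existing electronic data system and applied identically in both arms.
- For each screened smoking family that does not enter, record whether it was excluded (and on which item) or refused, and report these counts by arm.
- Complete consent and the baseline questionnaire before any advice is given.
- Name baseline hair nicotine and stage of change as covariates in the primary multilevel model, whatever the bivariate tests show.
- Where timing allows without extra staff, list eligible babies before teams are told their arm.

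**Cost:** a few fields in the form, a little time per screened family, and a sentence in the analysis section. Some families who are harder to follow will enter and may be lost. Unblinded teams will still seek consent, so the risk is reduced and not removed; the by-arm counts would let a reader judge what is left.

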### Sample size

Based on the data from the pilot study in 46 babies and using the same analysis technique of nicotine in hair used in the present study, a mean of 6.83 ng/mg and a standard deviation of 8.88 ng/mg have been obtained. Assuming a mean difference of 30% between the intervention group and the control group in nicotine in hair at the end of the intervention, with an alpha value of 0.05 and a power of 80%, 295 subjects are needed in each group. If we assume a loss of 20%, the sample size increases to 708 (354 in each group). It is considered feasible for each basic care unit to recruit eight babies in a period of two months. The estimates of the intra-cluster correlation coefficient in cluster randomized trials that evaluate the implementation of clinical practice guidelines using outcome variables in primary healthcare are generally less than 0.05 [34]. These intra-cluster correlation coefficients translate to a cluster size of eight in a design effect corresponding to a factor of 1.4. Therefore, the final simple size will be 992 babies (446 in each group).

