2. To estimate the adjusted effect, a multivariate multilevel model will be used. The dependent or principal variable is the child's exposure using the measure of nicotine in hair. The baby's age and sex, as well as the variables that have been shown to be statistically significant, will be included in the bivariate analyses. The basic care unit and the individual will be the levels in the multilevel analysis.

3. Concordance between the filled questionnaire and the nicotine collected in the hair: a summary evaluation of the questionnaire on a discrete, quantitative scale based on the data that is provided by the number of smoking cohabitants, the number of cigarettes that they smoke and the exposure time outside of the home. Pearson's (or Spearman's depending on the distribution) correlation coefficient will be calculated between the estimate and the result obtained in the nicotine hair analysis. The intraclass correlation coefficient will also be studied between both measures. Finally, both estimates will be dichotomized (questionnaire and nicotine in hair analysis) into two categories (exposed/not exposed) and the Kappa coefficient between the two will be calculated.

In all cases a bilateral alpha error of 0.05 and a 95% confidence interval will be used. To complete the explicit information, the comparison of means will be performed using a Student's t-test for parametric variables and the U Mann-Whitney test for non-parametric variables.

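### The final sample size is printed as 992 babies but 446 per group (which makes 892, very probably a misprint for 496), and the 20% loss is added by multiplying by 1.2 instead of dividing by 0.8

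*Protocol article*

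**What the plan says.** All the figures stand in the Sample size section of the protocol article.

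- The pilot data gave "a mean of 6.83 ng/mg and a standard deviation of 8.88 ng/mg have been obtained", from 46 babies.
- The target effect is set by "Assuming a mean difference of 30% between the intervention group and the control group in nicotine in hair". With alpha 0.05 and 80% power, the section arrives at 295 babies per group. The Statistical analysis section makes the test two-sided: "In all cases a bilateral alpha error of 0.05 and a 95% confidence interval will be used".
- Loss to follow-up comes next: "If we assume a loss of 20%, the sample size increases to 708 (354 in each group" in brackets.
- Clustering follows. Intra-cluster correlations (ICCs) are said to lie generally below 0.05, which the section translates for "a cluster size of eight in a design effect corresponding to a factor of 1.4".
- The last sentence gives the target: "Therefore, the final simple size will be 992 babies (446 in each group" in brackets.

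No other section gives a group size, a total or a number of teams.

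**The concern.** There are two separate faults.

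First, the total and the per-group figure disagree by 100 babies. Unequal allocation does not explain this, because the per-group figure is said to apply to each group and the earlier steps are all equal (295 each; 354 each, 708 in total).

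Second, the loss step uses the wrong operation. To keep 295 babies after losing a fifth, one divides by the fraction retained. Multiplying by 1.2 retains 1.2 x 0.8 = 0.96 of the target, 4% too few.

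This is the only statement of the final sample size. A reader cannot tell from that sentence which figure was planned, and the 80% power does not follow exactly from the steps shown.

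**Working it through.** **Inputs** (Sample size section unless noted): mean 6.83 ng/mg; SD 8.88 ng/mg; difference 0.30 x 6.83 = 2.049 ng/mg; alpha 0.05, two-sided (Statistical analysis section); power 80%; loss 20%; eight babies per team; ICC at its stated upper value of 0.05; design effect (DE) 1.4 as printed.

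**1. The starting figure reproduces.** n = 2 x (1.960 + 0.842)² x 8.88² / 2.049² = 294.8, so 295 per group. A one-sided test would give 233, so the two-sided reading is the right one.

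**2. The loss step.** 295 x 1.2 = 354, the printed figure. After 20% loss, 354 x 0.8 = 283.2, below 295. The correct step is 295 / 0.8 = 368.75, so 369.

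**3. The design effect.** 1 + (8 - 1) x 0.05 = 1.35. The printed 1.4 is slightly larger, which is conservative.

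**4. The final step.** 708 x 1.4 = 991.2, so 992: the printed total reproduces. 354 x 1.4 = 495.6, so 496 per group, and 2 x 496 = 992. The printed 446 does not reproduce:
- 2 x 446 = 892, which is 100 short of 992.
- 446 / 354 = 1.26, which is not the stated design effect.
- 354 x 1.35 = 477.9, so 1.35 does not give 446 either.
- 446 / 8 = 55.75 teams, whereas 496 / 8 = 62 whole teams.

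**5. Power at each group size.** Effective n per group = N x 0.8 / DE; power = Φ(2.049 / (8.88 x √(2 / effective n)) - 1.960). For example, 496 x 0.8 / 1.4 = 283.4, and Φ(2.747 - 1.960) = 78.4%.

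The third design effect below assumes that losses are spread over the teams, leaving 8 x 0.8 = 6.4 babies per team: 1 + 5.4 x 0.05 = 1.27.

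| Per group | DE 1.4 | DE 1.35 | DE 1.27 |
|---|---|---|---|
| 496: effective n | 283.4 | 293.9 | 312.4 |
| 496: power | 78.4% | 79.9% | 82.2% |
| 446: effective n | 254.9 | 264.3 | 280.9 |
| 446: power | 74.0% | 75.6% | 78.1% |

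**6. What a full 80% corresponds to on the corrected chain.** At DE 1.4: 295 x 1.4 / 0.8 = 516.25, so 517 per group (1,034 in total; power 80.1%). At DE 1.35: 295 x 1.35 / 0.8 = 497.8, so 498 per group (996 in total). Against 517, a group of 496 is 21 short; against 498, it is 2 short.

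**The case against.** The strongest reply is that 446 is a one-digit slip. The total, the preceding step and the design effect all point to 496, as does the whole number of teams. This stands, and it governs how the power figures should be read: 74.0% to 78.1% would apply only if 446 per group were really used, and nothing else in the article supports that figure.

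A reader might also infer that 446 sets the recruitment stop or the number of teams to randomise, so that the trial would close about 10% short. The article does not support this. Its Sampling strategy section limits recruitment by team (eight cases, within two months), and no section gives a number of teams or ties one to 446.

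The reply to the loss step is that it hardly matters at 992. This also largely stands. At 496 per group the shortfall is 1.6 points of power at 1.4 and 0.1 at 1.35. If losses thin the clusters to 6.4, power exceeds 80%. Moreover, 0.05 is given as an upper value for the ICC. Setting N x 0.8 / DE to 294.8 and solving for the ICC, 496 per group holds 80% up to about 0.049 with eight per team, or 0.064 with 6.4. For 446 the limits are about 0.030 and 0.039. A flat statement that the trial misses 80% power would therefore go too far.

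Neither reply removes the errors. The sentence still contradicts itself, and 354 still does not leave 295 after a 20% loss.

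**Conclusion.** The section is wrong as written on two counts. The figures 992 and 446 per group are incompatible by 100 babies; the article's own chain gives 496, and 446 is very probably a misprint. The loss allowance uses the wrong operation and leaves 283 of the 295 babies needed.

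The practical size is small if 496 was meant: 78.4% power at the stated design effect of 1.4, 79.9% at 1.35, and 82.2% if losses reduce teams to 6.4 babies. These figures take the article's mean, SD, 30% difference and 20% loss as given; the last two also assume an ICC of 0.05. The documents do not show a trial that will run at 74% power.

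The correction is still needed, because this is the article's only statement of its final target.

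**What to change.** Three edits to the Sample size section:

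1. Correct the last sentence to: *992 babies (496 in each group, 62 teams of eight per arm)*.
2. Show the loss step as 295 / 0.8 = 369 per group in place of 354 (708 in total).
3. Since the corrected steps no longer lead to 992, present 992 as the fixed total and state what it delivers with 20% loss: about 78% power at a design effect of 1.4, and about 80% at 1.35 (ICC 0.05, eight per team). Note that a full 80% would correspond to 517 per group at 1.4 or 498 at 1.35.

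Replacing 1.4 by 1.35 is optional, because 1.4 errs on the safe side. If 446 per group was in fact intended, the total must become 892 and the power be restated from the table above.

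The cost is a few numbers in one paragraph and a slightly less favourable stated power. No added enrolment is requested.
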